## 2 STUDY RATIONALE

### JUSTIFICATION FOR DOSE

#### Rationale for Dose Selection of KN026

The pre-specified dose of KN026 in this study is 30 mg/kg Q3W, which was mainly selected based on the safety and preliminary efficacy data from KN026-CHN-I-001 study (first-in-human study of KN026). The safety evaluation at 30 mg/kg dose level has been completed in KN026-CHN-I-001. KN026 was generally well tolerated by the subjects without DLT events. There were 3 subjects with confirmed PR and 5 subjects with unconfirmed PR, and the subjects with SD had varying degrees of reductions in the target lesions. The dose selection also referred to the approved doses of the same class of drugs trastuzumab and pertuzumab, as well as the clinical study data and recommended Phase 2 dose of the investigational drug ZW25 with the same action mechanism.

The action mechanism of KN026 was similar to trastuzumab in combination with pertuzumab. As described in the package inserts of trastuzumab, trastuzumab is used for metastatic breast cancer with an initial loading dose of 4 mg/kg and a weekly maintenance dose of 2 mg/kg, resulting in a steady-state trough level of 79 µg/mL; trastuzumab is used for adjuvant treatment of breast cancer with an initial loading dose of 4 mg/kg and a maintenance dose of 6 mg/kg every 3 weeks, resulting in a steady-state trough level of 63 µg/mL. As described in the package inserts for pertuzumab, pertuzumab is used for adjuvant treatment of breast cancer with an initial loading dose of 840 mg and a maintenance dose of 420 mg every 3 weeks, resulting in a steady-state trough level of 60-70 µg/mL. Therefore, we expected that the mean trough concentration levels of the effective dose of KN026 would also be within this range. In the Phase 1 dose escalation study of KN026, the dose levels with trough concentrations within the range of 60-80 µg/mL will be selected as the dose in Phase 2 clinical study. At present, we have obtained PK data of KN026 5 mg/kg and 10 mg/kg QW dose levels up to March 10, 2019, which showed that the pre-dose plasma concentration of KN026 in the 10 mg/kg QW dose group had reached the steady-state trough levels at the approved trastuzumab dose. The dose intensities of 30 mg/kg Q3W and 10 mg/kg QW were comparable.

Besides, the translational medicine researches of KN026 suggested that the effective concentration of KN026 was 20 µg/mL, and 60-80 µg/mL was the optimal tumor killing concentration range. A population PK model was constructed based on human PK data, and 1000 simulations of the target population were performed. The recommended Phase 2 dose was defined as that 90% or more of the simulated population reached the target concentration range of 60-80 µg/mL. Based on the clinical safety data, 20 mg/kg Q2W or 30 mg/kg Q3W was used as the recommended Phase 2 dose of KN026, and steady state would be reached at Week 8 (Q2W) or Week 9 (Q3W) after multiple doses (Figure 1 and 2).

A human PK-tumor growth model was constructed based on human pharmacokinetic and human efficacy data to analyze the correlation between PK and anti-tumor activity in humans. The analysis suggested that rapid maximal effective concentrations were associated with the optimal

antitumor activity, so a loading dose was designed. The steady-state concentrations would be reached in the first cycle of administration after the loading dose in Weeks 1 and 8 at 20 mg/kg Q2W (Figure 3), which was expected to further improve the efficacy.

[figure not shown]

Figure 1

[figure not shown]

Figure 2

In the investigator-initiated study KN046-IST-02, the safety and tolerability of KN026 in combination with KN046 were investigated in patients with advanced HER2-positive or HER2-expressing gastrointestinal tumors after failure of standard of care. The study results showed that KN026 30 mg/kg Q3W (loading dose on C1D1 and D8) + KN046 5 mg/kg Q3W was a safe and tolerable dose.

#### Rationale for Dose Selection of KN046

The pre-specified dose of KN046 for this study is 5 mg/kg Q3W. The rationale for dose selection was mainly based on the safety and preliminary efficacy data from the KN046-AUS-001 study (first-in-human study of KN046) and KN046-CHN-001 study (first-in-China study of KN046). The safety evaluation at 5 mg/kg Q2W has been completed in KN046-AUS-001 and the safety evaluations at 5 mg/kg Q2W and Q3W have been completed in KN046-CHN-001. KN046 was generally well tolerated by the subjects. Based on the *ex vivo* release data of IL-2 from tumor patients in KN046-CHN-001 clinical study and corresponding KN046 drug concentration data, a PK (pharmacokinetic)/PD (pharmacodynamic) model was constructed to explore the correlation between drug concentration and *ex vivo* release of IL-2.

As of June 24, 2019, *in vitro* releasing data of IL-2 were obtained from 16 subjects, and a PK/PD model was constructed using R, with the model equation as:

$$E(C) = E0 - \frac{Imax \cdot (E0 - 1) \times C}{IC50 + C}$$

The corresponding Ctrough\_targets (IC95) were estimated from the point estimate of IC50 (138 ng/mL) and the upper limit of 95% CI (457 ng/mL), respectively. The corresponding Ctrough\_targets were 2,629 ng/mL and 8,683 ng/mL, respectively. Ctrough\_target was placed into the 3 mg/kg Q2W, 5 mg/kg Q2W and the fitted 5 mg/kg Q3W concentration-time curve. Since more than 75% of the dosing interval of 5 mg/kg Q3W per cycle was above Ctrough\_target, 5 mg/kg Q3W may be suitable for KN046 combination therapy.

KN046-IST-02 study has demonstrated that KN026 20 mg/kg Q2W + KN046 3 mg/kg Q2W is a safe and effective dose. Based on the data from Phase 1 studies of KN026 and KN046 and PK/PD study results, and considering that dosing every three weeks is more convenient in clinical practice, the dose of KN026 30 mg/kg Q3W + KN046 5 mg/kg Q3W is selected for this study. The safety data from the dose group KN026 30 mg/kg Q3W + KN046 5 mg/kg Q3W will be provided as further support before the subjects are enrolled in this study.

## **RATIONALE FOR PRIMARY STUDY ENDPOINTS**

The primary endpoints of this study are ORR and DOR as assessed by the investigator per RECIST 1.1. For early exploratory efficacy study, objective response and duration of response are acceptable surrogate endpoints for measuring clinical benefits and can reflect the drug's anti-tumor activity, especially when persistent anti-tumor response can be observed.

## **RATIONALE FOR INDICATION SELECTION**

The study will be conducted in designated tumor types, including HER2-positive gastric/gastroesophageal junction (GC/GEJ) cancer, HER2-positive breast cancer, HER2-positive non-small cell lung cancer, and other HER2-positive solid tumors. The rationale for selection of HER2-positive tumors is provided in Section 1.2.

## **BENEFIT-RISK ASSESSMENT**

The occurrence of AEs will be closely observed in the clinical study, including vital signs, ECG, laboratory blood and urine tests. Based on the preclinical studies of KN026 and clinical results of currently marketed anti-HER2 monoclonal antibody drugs with the same target, the most common adverse reactions included pyrexia, nausea, vomiting, infusion-related reactions, diarrhea, infection, cough aggravated, headache, asthenia, dyspnea, rash, neutropenia, anemia, and myalgia. Most were mild to moderate in severity. Adverse reactions requiring interruption or discontinuation of anti-HER2 monoclonal antibody therapy included congestive heart failure, significant decrease in left ventricular function, severe infusion reactions, and pulmonary toxicity. Close monitoring and specific targeted treatment measures are necessary. Based on relevant ESMO and NCCN guidelines and the principles of toxicity management in expert consensus, this study will reduce the potential risks of subjects with measures such as exclusion criteria, safety monitoring, initial dose design, treatment interruption provisions, discontinuation criteria, and management of toxicity related to anti-HER2 monoclonal antibody drugs (Sections 6.1.4, 6.2.3.2 and 6.2.3.3). The management of potential infusion reactions and hypersensitivity reactions during use of KN026 as a biological product is described in Section 6.2.3.1.

Based on preclinical studies of KN046 and clinical results of marketed anti-PD-L1 and anti-CTLA-4 monoclonal antibody drugs with the same target, the most common adverse reactions included tiredness, infusion reaction, diarrhea, arthralgia, rash, nausea, pruritus, and headache, most of which were mild to moderate in severity. Autoimmune-related toxicities may occur during drug treatment with anti-PD-L1 and anti-CTLA-4 monoclonal antibodies, therefore close monitoring and special therapeutic measures are required. These drug-related AEs included rash and pruritus

in the skin system, diarrhea and colitis in the gastrointestinal system, hypophysitis, hepatitis, endocrine disorders, pneumonia, and renal insufficiency. In this study, principles for the management of immune-related toxicities will be developed with reference to relevant ESMO and NCCN guidelines. Measures such as exclusion criteria, safety monitoring, initial dose design, treatment interruption, discontinuation criteria, and management of immune-related toxicities will be taken to reduce the potential risks of subjects (Section 6.1.4, Appendix 4). The management of potential infusion reactions and hypersensitivity reactions during use of KN046 as a biological product is described in Section 6.2.3.1. As ADCC function is retained in the structure of KN046, the management of potential tumor lysis syndrome is described in Section 6.2.3.4.

The study will be conducted in compliance with the protocol, GCP, the Declaration of Helsinki and other relevant regulations.

### **3 STUDY OBJECTIVES AND STUDY ENDPOINTS**

#### **STUDY OBJECTIVES**

##### **Primary Objective**

- To evaluate the anti-tumor activity of KN026 in combination with KN046 in patients with HER2-positive solid tumors;

##### **Secondary Objectives**

- To evaluate the safety and tolerability of KN026 in combination with KN046;
- To evaluate the effect of HER2 amplification on the efficacy of KN026 in combination with KN046 (as supported by data);
- To evaluate the effect of HER2 expression levels (IHC1+ vs. IHC2+ vs. IHC3+) on the efficacy of KN026 in combination with KN046;
- To evaluate the effect of KN026 and KN046 drug exposure levels on anti-tumor activity;
- To evaluate immunogenicity of KN026;
- To evaluate immunogenicity of KN046.

##### **Exploratory Objectives**

- To evaluate the effect of PD-L1 expression, TIL, and TMB/GEP on the efficacy of KN026 in combination with KN046; to evaluate the correlation between HER2/CDK12 co-amplification and clinical efficacy variables in the breast cancer cohort.

#### **STUDY ENDPOINTS**

##### **Primary Endpoints**

- Objective response rate (ORR) and duration of response (DOR) as judged by the investigator per RECIST 1.1 criteria

##### **Secondary Endpoints**

- Progression free survival (PFS), progression-free survival rate (PFSR) at 6 and 12 months, clinical benefit rate (CBR; defined as CR, PR, or SD  $\geq$  24 weeks) as judged by the investigator according to RECIST 1.1 criteria;
- Overall survival (OS), overall survival rate (OS rate) at 6 and 12 months;
- Frequency and severity of adverse events (AEs) (NCI CTCAE 5.0); changes in vital signs, physical examinations, electrocardiograms, and safety laboratory measures;
- Correlation between biomarkers (HER2 IHC, HER2 amplification) and clinical efficacy variables (ORR, CBR, PFSR, etc.);

Version No.: 4.2

- Correlation of KN026 and KN046 exposure levels ( $C_{\max,ss}$ ,  $AUC_{ss}$ ,  $C_{\text{trough},ss}$ ,  $C_{\text{avg},ss}$ , etc.) with efficacy variables (ORR, DOR, CBR, etc.) and safety variables (QTc and LVEF);
- Incidence and titer of anti-KN026 antibody (ADA); incidence of KN026 neutralizing anti-drug antibody (NADA) in subjects with high ADA titer;
- Incidence and titer of anti-KN046 antibody (ADA); incidence of KN046 neutralizing anti-drug antibody (ADA) in subjects with high ADA titer.

#### **Exploratory Endpoints**

- The correlation between biomarkers (PD-L1 expression, TIL, and TMB) and clinical efficacy variables (ORR, CBR, PFSR, etc.); the correlation between HER2/CDK12 co-amplification and clinical efficacy variables in the breast cancer cohort.

## 4 STUDY DESIGN

### OVERALL STUDY DESIGN

This study is an open-label, Phase 2, multicenter clinical study to evaluate the efficacy and safety of KN026 in combination with KN046 in subjects with HER2-positive solid tumors.

The study will include:

Three different cohorts of HER2-positive solid tumors treated with KN026 30 mg/kg Q3W (loading dose on C1D1 and D8) in combination with KN046 5 mg/kg Q3W:

- HER2-positive gastric/gastroesophageal junction cancer (GC/GEJ), n = 30 to 60;
- HER2-positive breast cancer (BC), n = 30 to 36;
- Other HER2-positive solid tumors, n = 20 to 26.

HER2-positive is defined as follows:

- HER2 IHC3+ (ASCO/CAP 2018; Wolff et al, 2018); **or**
- HER2 gene amplification (ISH+: HER2/CEP17 ratio > 2 or HER2 gene copy number > 6; or NGS: HER2 gene copy number > 6).

All subjects will be required to submit slides for central laboratory review of HER2 status at screening. Subjects who have received HER2-targeted therapies such as trastuzumab should provide tumor tissue samples collected after failure of HER2-targeted therapy for determination of HER2-positive status.

The study is divided into a screening period (Day -28 to -1), a treatment period, the end-of-treatment (EOT) follow-up visit, a 30-day safety follow-up visit, a 90-day safety follow-up visit, and a survival follow-up visit.

Subjects will undergo tumor imaging assessments at screening and every 6 weeks ( $\pm$  7 days) after the dose of study drug. After 48 weeks, the frequency of imaging assessments will be adjusted to every 12 weeks ( $\pm$  7 days) until disease progression per RECIST 1.1, initiation of a new anti-tumor therapy, or subject withdrawal of consent, whichever occurs first. When an objective response defined in RECIST 1.1 occurs, confirmation by imaging should be performed no earlier than 4 weeks and no later than 8 weeks.

Each subject will receive KN026 in combination with KN046 per protocol until radiographic progression per RECIST 1.1, intolerable toxicity, or withdrawal of consent, whichever occurs first. After the investigator first judges the subject condition as PD per RECIST v1.1 criteria, if the subject is clinically stable and does not experience intolerable toxicity during the treatment, the subject will be allowed to continue treatment with KN026 + KN046 until PD is confirmed. Clinical stability is defined as: stable ECOG PS score, no unacceptable toxicity associated with treatment of KN026 and/or KN046, no rapid PD requiring other salvage therapy, and no acute conditions requiring urgent medical intervention due to PD (e.g., central nervous system metastases, dyspnea due to tumor compression of the airway, spinal cord compression, etc.). The

clinical, oncology, and laboratory evaluation flow of each study period is detailed in Table 1 and 2 as well as Section 7.

### **End of Study Definition**

The end of the study is defined as 1 year after the last dose of all subjects; the completion of the last study-related telephone contact or visit, withdrawal from the study or lost to follow-up (i.e., the investigator is unable to contact the subject) of the last subject; death or premature withdrawal from the study of all subjects; or the sponsor assesses that the study has met the study expectations (e.g., completion of the primary endpoint assessments), whichever occurs first.

### **Premature Study Termination**

The study may be prematurely discontinued if:

- New information suggests an unacceptable risk-benefit ratio for the investigational product;
- The sponsor decides to terminate the study and/or a cohort based on the consideration that it is no longer appropriate to continue the study from the medical and ethical perspective;
- It is not possible to complete the study within an acceptable time period due to poor enrollment of subjects. The sponsor may decide to terminate the study of a cohort if the enrollment of a cohort is poor and the likelihood of study completed within an acceptable timeframe is low;
- The sponsor decides to discontinue the development of the investigational product.

If the study is terminated prematurely, the subject should receive a visit as soon as possible and complete the visit as required by Section 7.1.3. For the sake of protecting the subjects, the investigator may be asked to conduct additional visits.

After termination of the study, the regulatory authorities and the Independent Ethics Committee (IEC)/Institutional Review Board (IRB) will be notified in accordance with applicable regulations.

Regulatory authorities may also request suspension or termination of the whole study.

### **INTERIM ANALYSES**

The primary efficacy analysis may be performed at the end of all cohorts (defined as "enrollment completed and at least 2 postbaseline oncology evaluations completed").

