| Tumor imaging (thoracic/abdominal/pelvic)                            | X                 | Every 6 weeks (± 7 days); from 48 weeks onwards: every 12 weeks (± 7 days)                            |  |  |  |  |  | (X) | (X)              | (X) | (X)                        |  |
| Tumor imaging (brain, if applicable)                                 | (X)               | (if clinically indicated)                                                                             |  |  |  |  |  |     |                  |     |                            |  |
| Bone scan (if applicable)                                               | (X)               | (if clinically indicated)                                                                             |  |  |  |  |  |     |                  |     |                            |  |

| Study Drug Administration                |  |   |   |  |   |  |  |                            |  |  |  |  |
|------------------------------------------|--|---|---|--|---|--|--|----------------------------|--|--|--|--|
| KN046 administration (Q3W)  |  | X |   |  | X |  |  | Administration on Day 1/21 |  |  |  |  |
| KN026 administration (Q3W)  |  | X | X |  | X |  |  | Administration on Day 1/21 |  |  |  |  |

1 The EOT visit may be performed on the day of the decision to discontinue KN026 and KN046 treatment, and the same EOT test may not be repeated if it is performed within 7 days after the last pre-treatment evaluation;

2 The 30- and 90-day safety follow-up visits will be performed after the end of all study treatments. For subjects who discontinue KN046 treatment first and continue to receive KN026, the 90-day safety follow-up visit is not required if 30 days after the last dose of KN026 are later than 90 days after the last dose of KN046;

3 All concomitant medications/procedures from 28 days prior to dosing to 30 days after the last dose of KN046 and/or KN026 should be recorded. Concomitant medications/procedures after the 30-day safety follow-up period are also to be recorded as part of SAE recording, analysis, and reporting if they are performed for the purpose of treating SAEs related to KN046 and/or KN026;

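### Section 4.2 permits the primary analysis after two post-baseline scans, too early to confirm week-12 responses or to judge DOR in late enrollees, and the end-of-study rule could leave 12-month PFS and OS rates unobserved

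*Protocol*

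**What the plan says.** - **Trigger.** Section 4.2, headed Interim Analyses, says the primary efficacy analysis may be done at the end of all cohorts, defined as "enrollment completed and at least 2 postbaseline oncology evaluations completed". No other maturity condition, minimum DOR follow-up or later DOR data cut is stated.
- **Scans.** Table 1 and Section 7.2.2.3 schedule imaging every 6 weeks (± 7 days), and every 12 weeks after week 48.
- **Primary endpoints.** Section 3.2.1: "Objective response rate (ORR) and duration of response (DOR) as judged by the investigator per RECIST 1.1 criteria". Section 2.2 justifies them "especially when persistent anti-tumor response can be observed".
- **Confirmation.** Section 4.1: "confirmation by imaging should be performed no earlier than 4 weeks and no later than 8 weeks". Table 1, footnote 12, gives the same window.
- **Analysis.** Section 9.5 reports ORR as a proportion with a Clopper-Pearson interval on the Safety Set, and DOR by Kaplan-Meier, both by cohort.
- **Landmark endpoints.** Section 3.2.2 lists "Overall survival (OS), overall survival rate (OS rate) at 6 and 12 months", and PFS rates at the same times.
- **End of study.** Section 4.1.1 lists several conditions, the last being "or the sponsor assesses that the study has met the study expectations (e.g., completion of the primary endpoint assessments), whichever occurs first". Sections 7.1.5 and 7.1.6 repeat this condition. Under Section 7.2.2.3 tumor evaluation stops at the end of the study. The note in Section 7.1.6 then provides for continued drug supply and some safety follow-up, and names no efficacy follow-up.

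**The concern.** The only stated maturity condition is shorter than the protocol's own endpoints need. ORR is a simple proportion of all treated subjects, so it does not adjust for short follow-up as Kaplan-Meier does. If only confirmed responses count, one that is not yet confirmed or not yet seen enters as a non-response, and ORR is biased downward. DOR is a primary endpoint valued for persistence, yet late enrollees contribute very little duration.

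The end-of-study rule can make this permanent. If the sponsor judged the primary assessments complete soon after an early analysis, tumor and survival follow-up could stop and the 12-month rates would rest on early enrollees. In an open-label trial with investigator-assessed response, a low and permissive floor also leaves the choice of cut-off open.

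**Working it through.** **The plan's own figures.** The protocol gives no figure for accrual duration, analysis timing or DOR precision. The nearest yardstick is the sample-size table in Section 9.2, where 12 responders of 30 (40%) have a 95% interval of 22.7% to 59.4%. Exact Clopper-Pearson limits reproduce this.

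**Calendar arithmetic (protocol inputs only).**
- Post-baseline scans 1 and 2 fall at weeks 6 and 12; the visit window puts scan 2 between weeks 11 and 13.
- A response first seen at week 12 can be confirmed at 12 + 4 = week 16 to 12 + 8 = week 20; the next scheduled scan is week 18. All are after the floor.
- A response first seen at week 6 in the last subject has at most 12 − 6 = 6 weeks of observed DOR.
- 12-month rates need about 52 weeks in the last subject, which is 52 − 12 = 40 weeks after the floor.

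Section 7.2.2.3 words the confirmation timing in a self-contradictory way (six weeks later, yet inside four weeks). I used the 4 to 8 weeks of Section 4.1 and Table 1; the texts must be reconciled.

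**Assumptions for the size.** Uniform accrual over A weeks (6, 12 or 18 months = 26.09, 52.18 or 78.27 weeks); cut-off at the last subject's week 12; ORR 40%; first response at weeks 6/12/18/24 in 60/25/10/5% of responders; confirmation at the next scheduled scan; ORR counts confirmed responses only. None of these is given in the protocol.

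**ORR loss.** A subject who starts u weeks before the last one has 12 + u weeks of follow-up. Confirmation at weeks 12, 18, 24 or 30 needs u of at least 0, 6, 12 or 18. The share of responders missed is

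(0.25×6 + 0.10×12 + 0.05×18)/A = 3.6/A.

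Times 40 points: 5.5, 2.8 and 1.8. A simulation of the same set-up (n = 30, 1,500 trials per scenario) gives 5.5, 2.8 and 1.9.

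With the floor moved to week 18, the share is (0.10×6 + 0.05×12)/A = 1.2/A, or 1.8, 0.9 and 0.6 points.

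**Follow-up and DOR maturity at the two-scan floor.**
- Subjects with at least 12 months' follow-up: (12 + A − 52.18)/A, not below 0. This reaches zero at A = 40.18 weeks, about 9 months.
- Responders with a DOR event: the average of 1 − exp(−λ(6 + u)) over u from 0 to A, with response at week 6, exponential DOR and λ = ln 2 / median.
- Confirmed responders with at least 6 months' potential DOR follow-up use the response timing above. For A = 6 months only week-6 responders with u of at least about 20 weeks qualify: 0.60×6/26.09 = 0.138. Divided by the confirmed share, 1 − 0.138 = 0.862, this is 16%.

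| Accrual (assumed) | ORR points lost | Confirmed responders with ≥ 6 months' potential DOR | Subjects with ≥ 12 months | DOR events, median DOR 6 months | DOR events, median DOR 12 months |
|---|---|---|---|---|---|
| 6 months | 5.5 | 16% | 0% | 38% | 22% |
| 12 months | 2.8 | 58% | 23% | 54% | 33% |
| 18 months | 1.9 | 73% | 49% | 64% | 43% |

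**With a cut 26 weeks later** (week 38 for the last subject), every response first seen by week 24 can be confirmed by week 30, so no ORR loss remains under these assumptions. A last-enrolled responder at week 6 or 12 has 32 or 26 weeks of potential DOR. The share of responders with at least 6 months is 1 − 1.2/A, about 95% to 98%.

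**The case against.** Several counter-arguments have force.

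- **The rule is permissive.** A reader might infer that the protocol fixes the primary analysis at two scans and so cannot deliver DOR. The text does not support that: it says the analysis may be performed, and two scans is a minimum. Only late enrollees are short of follow-up, Kaplan-Meier uses the longer follow-up of earlier subjects, and scanning continues after the analysis unless the study is ended. This stands.
- **The trigger waits for all cohorts.** Cohorts that fill early are more mature than a single-cohort calculation shows; the worst case is the last cohort to fill. This stands.
- **Confirmed ORR is an inference.** Sections 3.2.1 and 9.5 do not say that only confirmed responses count. The 16.7% quoted in Section 1.4.3 for KN046-AUS-001 equals 7/42, and its 7 responders include 4 unconfirmed partial responses. This stands, so the ORR loss is conditional.
- **The ORR loss is small beside sampling error.** A loss of 1.9 to 2.8 points with 12 to 18 months' accrual is minor against an interval from 22.7% to 59.4%. This stands, although the loss has a known direction.
- **Closure needs a separate decision.** A reader might infer that the study is planned to close at about week 12. It is not. DOR is itself primary, so completing the primary assessments can reasonably be read as including it. That holds in part: the protocol does not say when DOR assessment is complete, the wording is only an example within a sponsor judgement, and nothing ties closure to the 12-month endpoints.
- **This is SAP material in a descriptive Phase 2 trial.** The SAP may set a later cut-off, and with no hypothesis test no false-positive claim is at stake. But the protocol itself states the floor and the end-of-study rule, and an SAP would not change Sections 4.1.1, 7.1.5 and 7.1.6.

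**Conclusion.** The concern holds as a floor set too low together with a closure condition left too open. From the protocol's own schedule, without assumptions, the earliest permitted analysis precedes confirmation of a week-12 response in the last subjects and gives their week-6 responders at most 6 weeks of DOR.

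The overall size depends on accrual and response timing, which the protocol does not give. Confirmed ORR loses about 2 to 5.5 points over 6 to 18 months' accrual. The share of responders with a DOR event ranges from 22% to 64% over the same accrual and median DOR of 6 to 12 months. If the study were closed at the floor, no subject would have 12 months of follow-up with accrual of about 9 months or less, and about half would with 18 months. The DOR and closure limbs matter more than the ORR limb, since follow-up lost at closure may not be recoverable.

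**What to change.** **Section 4.2.**
- Set the earliest primary ORR analysis when every subject has had the opportunity for at least three post-baseline scans (week 18, plus the confirmation window for a week-12 response), or has progressed, died or left.
- Label any two-scan look, and DOR at that look, as interim and descriptive.
- Set a main DOR data cut at a fixed calendar point, for example about 6 months after the last subject's week-12 scan.

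A rule that every responder must have 6 months of follow-up is not advised. A last-enrolled subject responding at week 18 or 24 would reach it at about week 44 or 50, which is 32 to 38 weeks (about 7 to 9 months) after week 12, and still later responders would extend the wait without limit.

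**Sections 4.1.1, 7.1.5 and 7.1.6.** Allow the sponsor-judgement condition only after the main DOR cut and 12 months' potential follow-up of the last subject. Do not limit termination for safety or the other reasons in Section 4.1.2.

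**Cost.** Relative to the earliest dates now permitted, the primary ORR readout moves by about 6 to 8 weeks, the main DOR readout by about 6 months and the earliest sponsor-judged closure by about 40 weeks. No patients or new visit types are added, because the scans and survival contacts are already scheduled. A week-18 floor still leaves up to about 1.8 ORR points unconfirmed under the 6-month accrual assumption, which the later DOR cut would recover.
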